#### Control group: standard YMCA membership

The control group will receive a 12-week complimentary YMCA membership and the frequency of attendance to engage in exercise will be self-determined. As part of this membership, participants will have access to eight fitness coaching sessions to receive instruction about the use of equipment or exercise regimes. These coaching sessions will be provided by YMCA staff who we will train to work with individuals with stroke but are not involved in the FIT for FUNCTION program. The standard YMCA membership was chosen as the control intervention since it reflects what is currently available as an option for people with stroke wanting to participate in community-based exercise programming in the region.

### Assessments

Before the initial assessment, the assessor will obtain written consent from each participant. Data will be entered directly into the database at the time of assessment using a tablet with a remote connection to REDCap, a secure web-based data management system. All assessments will take place at the YMCA with a physiotherapist trained in the administration of the outcome measures and in the use of REDCap.

Results from the pilot study confirm that the assessment sessions took approximately 90 min per participant and the sessions were generally well tolerated. At baseline, participant demographics will be recorded, along with stroke severity (NIH Stroke Scale), stage of recovery (Chedoke-McMaster Stroke Assessment), and co-morbidity and illness severity (Cumulative Illness Rating Scale) [57]. Cognitive impairment (MoCA) [58], presence of depressive symptoms (Centre for Epidemiologic Studies Depression Scale) [59, 60], and self-reported falls will be documented at baseline, 12 weeks, and 24 weeks along with the assessment of the primary and secondary outcomes (Fig. 2).

**Fig. 2 Fig2:**
[figure not shown]
Schedule of enrolment, interventions, and assessments. MOCA Montreal Cognitive Assessment, CES-D Centre for Epidemiological Studies Depression Scale, CIRS-G Cumulative Illness Rating Scale for Geriatrics, NISS National Institutes of Health Stroke Scale, RNLI Reintegration to Normal Living Index, 10 MWT, Ten-meter walk test, CMSA Chedoke-McMaster Stroke Assessment, BBS Berg Balance Scale, EQ5D-5L European Quality of Life 5-Dimension Questionnaire, RAPA Rapid Assessment of Physical Activity, PAM Patient activation measure, Bloodwork Glucose, insulin, HbA1c, triglycerides, cholesterol, cholesterol/HDL ratio, non-HDL cholesterol, C-reactive protein

### Primary outcome

#### Community reintegration

The RNLI assesses the degree to which individuals who have experienced traumatic or incapacitating illness achieve reintegration into normal social activities (e.g. recreation, movement in the community, and interaction in family or other relationships) [61]. It has good content validity (Cronbach’s Alpha [*r* > 0.90]) and sensitivity to change [62]. Seven out of 11 items showed substantial test–retest reliability (kappa > 0.61) [63].

### Secondary outcomes

#### Level of physical activity

The Rapid Assessment of Physical Activity (RAPA) is a nine-item measure that assesses frequency and intensity of aerobic physical activity and frequency of strengthening and flexibility exercises [64]. Compared to a criterion standard, the Community Healthy Activities Model Program for Seniors [64], the RAPA is more highly correlated (*r* = 0.54) with moderate caloric expenditure than the Patient-centered Assessment and Counselling for Exercise (*r* = 0.44) [65]. It has a reported sensitivity (81%) and positive predictive value (77%) [64].

We will also include accelerometry to quantify activity counts as an objective measure of habitual physical activity (Actical System, Philips Respironics, Bend OR, USA). The Actical is a small (29 × 37 × 11 mm), lightweight (16 g) omnidirectional accelerometer that measures activity counts via vibrations, which are converted into step counts and time spent in four activity levels [66]. It will be secured to the ankle using a nylon strap and worn for three consecutive days (from Friday to Sunday to capture weekdays and weekend days). The accelerometry data will form part of the more comprehensive profile of cardiovascular health that will capture physical activity levels, resting blood pressure and HR, lipid profiles, glucose, and inflammatory markers.

#### Balance

We will use the BBS to assess dynamic and static balance and risk of falls. It has excellent reliability for both acute stroke (intraclass correlation coefficient [ICC] = 0.95) [67] and chronic stroke (ICC = 0.98) [68]. In patients with stroke and residual gait deficits, the minimal clinically importance difference was detected as 5.8 points [69, 70].

#### Physical functioning

The SPPB will be used to quantify lower extremity function by evaluating the time to walk 8 feet, standing balance, and repeated chair stands. A validation study showed an association between the performance of each of these tests and self-reported disability [71]. The 6MWT provides an indicator of exercise capacity by measuring the distance walked in 6 min [72]. The test–retest reliability of this test has been established in people with stroke (ICC = 0.973) and the minimal detectable change is 54.1 m [73]. Several studies have demonstrated the responsiveness of 6MWT distance after gait-targeted interventions with individuals with stroke [15, 74, 75]. Resting HR and blood pressure as well as a rate of perceived exertion (RPE) and fatigue level (0–10) are measured before commencing the 6MWT. Grip strength and isometric knee extension strength will be measured using hand-held dynamometry. For both tests, the average of three trials will be calculated. Handgrip has been shown to correlate with elbow flexion strength, knee flexion strength, and trunk extension strength [76].

#### Health-related quality of life

The European Quality of Life 5-Dimension Questionnaire (EQ-5D-5L) is a generic utility-based health-related QOL questionnaire [77]. It consists of five questions covering the dimensions of mobility, self-care, usual activities, pain/discomfort, and anxiety/depression with five response options indicating no, mild, moderate, severe, and extreme problems for each dimension [78]. The EQ-5D-5L defines a total of 3125 health states which can be converted to a utility index anchored at 0 for a state being equal to dead and 1 for full health. The utility index combined with life expectancy allows for the estimation of QALY, a recommended generic outcome measure in health economic evaluation in Canada (Canadian Drug and Technology Agency, Ontario Ministry of Health and Long-Term Care) and other countries (National Institute for Clinical Excellence, Australia Department of Health) [79–82]. The EQ-5D-5L is a prominent example of generic utility-based questionnaire with some indicators showing it is the most widely used in health economic evaluation [83]. The EQ-5D-5L has been validated in individuals undergoing stroke rehabilitation [84].

#### Cardiovascular health

HR and BP will be measured after 5 min sitting at rest. BP will be measured at the brachial artery of the unaffected arm. Two measurements will be taken and averaged. If values differed > 5 mmHg, two more readings were done and the average taken across four readings [85]. HR and BP will also be measured at the end of the 6MWT as indicators of cardiovascular response during sub-maximal exercise. Body mass, height, and waist and hip circumference will be measured and body mass index and waist:hip ratio calculated. Blood samples will be collected following 12-h fast for lipid profile (total cholesterol, high-density lipoprotein cholesterol, low-density lipoprotein cholesterol, triglycerides), glucose (glucose, insulin, glycated hemoglobin), and inflammatory markers (C-reactive protein).

#### Self-efficacy

Self-efficacy (SE) for physical activity will be assessed with a single question. Participants will be asked to rate how confident they are that they could participate in moderate intensity physical activity for 150 min per week on a scale of 1 (not confident) to 10 (very confident) [86]. Self-efficacy for managing chronic disease will be assessed using the Stanford Self-Efficacy for Managing Chronic Disease 6-Item Scale. This six-item scale is less burdensome for patients, containing items taken from several SE scales developed for the Stanford Chronic Disease Self-Management Program [87].

#### Self-management

The Patient Activation Measure (PAM) is a 13-item measure of the patient’s level of knowledge, skill, and confidence for self-management [88]. Cronbach’s alpha = 0.87 and test–retest reliability have been reported as high [89]. PAM scores were compared to three judges’ classification of the individuals’ level of activation with kappa = 0.8–0.9 as evidence of validity [59]. Test–retest reliability has been reported as ICC = 0.85 [90].

#### Healthcare utilization and costs

The healthcare resource utilization will be evaluated using a case report form (CRF) specifically developed for the economic evaluation. Relevant healthcare resource utilization will include specialist visits, family physician visits, emergency room visits, hospitalization, and medication related to stroke over the 24-week trial period. These resource utilizations will be converted to direct medical costs using appropriate unit costs from available public databases such as Ontario Health Insurance Plan, physician fee schedule, and Ontario Case Costing Initiative. Other relevant direct non-medical costs include the time of the kinesiologist and fitness instructor who will provide group exercise sessions, the cost of delivering eight-session group self-management education program by LWS-trained YMCA staff, the cost of three-month YMCA membership, the cost of developing the education materials, and the cost of transportation to and from the YMCA. Indirect costs may include the time of informal caregiver if any to provide assistance to the participating patient.

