#### Research questions and specific hypotheses

The proposed trial aims to answer the following research questions:Is the 12-week FIT for FUNCTION stroke program more effective than a standard YMCA membership in improving community reintegration (primary outcome) at 12 and 24 weeks?

*Hypotheses:* Participants in the FIT for FUNCTION group will demonstrate greater post-program improvement in community integration. Gains will be maintained at 24 weeks (12 weeks following program completion).2.Is the FIT for FUNCTION stroke program more effective than a standard YMCA membership in increasing levels of physical activity and improving physical functioning (walking, balance, strength), health-related QOL, cardiovascular health, and self-management at 12 and 24 weeks?

*Hypotheses:* Participants in the FIT for FUNCTION group will demonstrate greater post-program improvement in physical activity, physical functioning, health-related QOL, cardiovascular health, and self-efficacy. Gains will be maintained at 24 weeks (12 weeks following program completion).3.Is the FIT for FUNCTION program more cost-effective than a standard YMCA membership?

*Hypotheses:* Participants in the FIT for FUNCTION program will have lower direct and indirect medical costs over the 24 weeks of the trial period as evidenced by fewer hospital and physician visits, and formal and informal caregiver services. The costs associated with the FIT for FUNCTION program will be less than those for the control group. We also hypothesize that the FIT for FUNCTION program will be more effective in improving health-related QOL of participants.4.What participant characteristics are associated with degree of program response observed?

*Hypotheses:* Participants who demonstrate greater improvement in community integration (primary outcome) from the FIT for FUNCTION program will have less co-morbidities, illness severity, depressive symptoms, mobility, and cognitive impairment.

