#### Intervention group: FIT for FUNCTION

The 12-week FIT for FUNCTION program comprises an exercise component (2×/week group classes, 1×/week independent exercise) and a self-management / education component (1×/week).Exercise: group exercise sessions (60 min, 2×/week) will be delivered by a kinesiologist trained to work with individuals with stroke. A stroke rehabilitation physiotherapist will provide on-site consultation 4 h per week and remote consultation 3 h per week. These group classes were adapted from the Community-Based Exercise Program for Persons Living with Stroke [56] and a DVD training package was developed for staff as a standardized competency-based approach. The exercise classes comprise: (i) warm up (10 min); (ii) task-oriented strengthening and cardiovascular conditioning (20 min); (iii) mobility and balance (20 min); and (iv) cool down (10 min). The feasibility of this program was established in the pilot study, with no adverse events and four participants (6.6%) withdrawing from the program (one related to the intervention and three unrelated to the intervention). From the pilot study, we found that maintaining a class size of 12 and a staff:participant ratio of 1:4 was important for ensuring safety of all participants. See Additional file 4 for a detailed description of the exercise program.

Of note, the cardiovascular conditioning component will be enhanced in this proposed trial. Individualized prescriptions will be determined using HR reserve and rating of perceived exertion methods that we have used extensively in previous stroke trials [37, 39]. Participants will also attend an independent exercise session (1×/week), where they will have full access to equipment and facilities at the YMCA.

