#### Cost-effectiveness analysis

The cost-effectiveness analysis will compare the incremental cost and effectiveness of the YMCA-based FIT for FUNCTION program with the standard YMCA membership for stroke survivors, from both the public healthcare payer’s perspective and the societal perspective. Effectiveness will be measured with QALY, using the utility values calculated from the EQ-5D-5L with duration. The main summary measure for the cost effectiveness analysis will be the incremental cost per QALY gained over the 24-week duration of the trial. Given that this cost-effectiveness analysis is conducted alongside the trial, non-parametric bootstrap will be used to calculate the 95% CI around the incremental cost per QALY ratio. The decision uncertainty will be presented using cost effectiveness acceptability curves, which show the probability of the intervention being cost-effective compared with the control group at specified societal willingness-to-pay for a QALY. The economic analysis will be conducted in using Statistical Analysis Software 9.2.

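### The listed cost items do not secure the caregiver part of the cost hypothesis or the societal perspective, and they omit the programme's physiotherapist time

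*Protocol article*

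**What the plan says.** Four sections of the protocol article bear on this.

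- **Research questions and specific hypotheses** (question 3) predicts lower direct and indirect costs in the programme arm over 24 weeks, "as evidenced by fewer hospital and physician visits, and formal and informal caregiver services". It adds: "The costs associated with the FIT for FUNCTION program will be less than those for the control group".
- **Healthcare utilization and costs** describes a "case report form (CRF) specifically developed for the economic evaluation". The resource use to be collected is "specialist visits, family physician visits, emergency room visits, hospitalization, and medication related to stroke over the 24-week trial period". Non-medical items follow: kinesiologist and instructor time, delivery of the education sessions, the membership, development of the education materials, and travel. The section closes with: "Indirect costs may include the time of informal caregiver if any to provide assistance to the participating patient".
- **Analyses** states the hypothesis for question 3 again, this time as fewer hospitalizations and physician visits, with no mention of caregivers.
- **Cost-effectiveness analysis** compares the arms "from both the public healthcare payer’s perspective and the societal perspective".

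On programme staffing, **Intervention group: FIT for FUNCTION** says: "A stroke rehabilitation physiotherapist will provide on-site consultation 4 h per week and remote consultation 3 h per week". **Control group: standard YMCA membership** gives control participants eight coaching sessions as part of the membership.

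**The concern.** A cost hypothesis can be examined only on items that are collected. Here the hypothesis names caregiver services, formal and informal, as part of its evidence. The costing section does not name the first and leaves the second open. Informal caregiver time is also the only indirect cost that the section names. If it is not collected, the societal analysis has no listed indirect cost, and the prediction about indirect costs has nothing behind it. Caregiver hours that were not asked about during follow-up are hard to recover afterwards.

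The physiotherapist is a different kind of gap. The consultation is a programme-only input with hours fixed by the protocol. The costing list goes into enough detail to include education materials and travel, yet does not name it. One of the stated hypotheses is that programme costs will be below those of the control group, so an uncosted programme input bears directly on that comparison and on the incremental cost per QALY.

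**Working it through.** The document gives no cost figure to reproduce. The check is a comparison of sections, a sign check, and one short calculation.

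**1. Hypothesis against listed items**

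| Evidence named in the hypothesis | In Healthcare utilization and costs? | In the restated hypothesis (Analyses)? |
|---|---|---|
| Hospital visits | Yes | Yes |
| Physician visits | Yes | Yes |
| Formal caregiver services | Not listed | No |
| Informal caregiver services | Left at may include | No |

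Two of the four are secured, one is left open and one is absent. The document also carries two versions of the hypothesis for question 3.

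**2. Perspective against listed items**

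The payer analysis has its main inputs: visits, admissions and medication. It is touched by the missing formal care only so far as that care is publicly funded, which the document does not say. The societal analysis also needs indirect costs, and the one named item is the one left open.

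**3. Sign of the effect on incremental cost (programme minus control)**

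- If the trial's own hypothesis is true, programme participants use less formal and informal care. Leaving care out removes a saving and works against the programme.
- If caregivers spend extra time on the programme (the education sessions are aimed at caregivers as well as survivors), leaving informal care out works in favour of the programme.
- Physiotherapist time falls on the programme arm only, so leaving it out understates programme cost.
- If the membership price does not cover the control arm's coaching sessions, leaving those out understates control cost.

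The caregiver items therefore have no determined direction. The physiotherapist item, taken alone, does.

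**4. Size of the physiotherapist item**

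Inputs: 4 h on site and 3 h remote per week, 12 weeks, and the class size of 12 carried over from the pilot (all from the intervention section).

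- Weekly: 4 + 3 = 7 h.
- Per 12-week cycle: 7 × 12 = 84 h.
- Serving one class of 12: 84 / 12 = 7 h per participant.
- Shared by two classes: 84 / 24 = 3.5 h per participant.
- Shared by three classes, for example one at each site: 84 / 36 = 2.3 h per participant.

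The document does not say whether the 7 h are per class, per site or overall, hence the range. It gives no hourly rate. At an assumed 40 to 80 dollars an hour, 7 h is 280 to 560 dollars per programme participant, and 2.3 h (84 / 36) is about 93 to 187 dollars.

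**The case against.** The strongest reply is that this is a journal article and the economic case report form is not shown. The list is introduced with include, which need not be exhaustive, and the form may already ask about home care and caregiver hours. The phrase if any may also mean only that some participants have no caregiver. This is fair, and nobody can say from the article what the form lacks. But the point does not rest on the form. The article's own statements of hypothesis, costed items and perspective do not agree, and the word may leaves collection open even on the kinder reading.

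It can also be said that hospital and physician use, direct costs and most programme costs are collected. That stands. A reader might infer that the cost hypothesis cannot be tested at all; the document does not support this, because only the caregiver part is unsecured.

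A reader might also infer that the omissions as a whole tilt the result towards the programme. The document does not support this either. Under the trial's own hypothesis the caregiver omissions work the other way, and the control coaching sessions are not named separately.

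Nor does the document support reading the stroke-related wording as excluding injury costs. In the list, the qualifier most naturally attaches to medication alone. No difference between arms in injuries is stated: the intervention section reports no adverse events in the pilot, and Data monitoring and auditing expects no harm in either arm. What remains there is a request for clarity.

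**Conclusion.** The concern holds as a mismatch between sections. Formal caregiver services are in the hypothesis and not among the costed items. Informal care is the only named indirect cost and is left open, although a societal analysis is promised. The hypothesis is stated in two forms. The direction of any resulting bias is not determined by the document.

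Separately, the list as written understates programme cost by the physiotherapist consultation: 84 h per 12-week cycle, or 7 h per participant if one class of 12 uses all of it, and proportionately less if it is shared. This assumes that the list is followed as printed and that the pilot's class size applies. Any dollar value depends on an hourly rate that the document does not give.

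The Objectives section ranks costs and cost-effectiveness as tertiary, and the primary outcome is untouched. The change is worth considering, but it is not essential to the trial's main conclusion.

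**What to change.** In Healthcare utilization and costs:

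- List formal caregiver services and informal caregiver hours as definite items, collected in both arms.
- Add physiotherapist consultation time to the programme cost, and say whether the weekly hours are per class, per site or overall.
- Confirm that the membership cost covers the control arm's eight coaching sessions, or cost them too.
- State whether the stroke-related restriction applies to medication only.

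Then give the hypothesis for question 3 the same components in the research questions and in Analyses.

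The cost is small: a few more questions on the form, some extra recall burden, and use of staffing hours already written into the protocol. Recruitment began in October 2014, so caregiver data for participants already followed may need retrospective questions or imputation, and the report should say so. If caregiver data were not collected, restrict the societal conclusion accordingly and drop the caregiver part from the hypothesis.

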### Qualitative methods

Individual interviews will be used to investigate the participant perceived impact of the intervention and to substantiate the quantitative results, helping to answer research questions 1 and 2. An independent, experienced facilitator will conduct the interviews, which will be recorded and transcribed verbatim. We have utilized interview results from the pilot study to make modifications to the program and its processes.

